## Background

Rib fractures are common injuries in both trauma and non-trauma centers, occurring in up to 10–39% of patients with blunt chest trauma and accounting for 10% of all trauma admissions [1–4]. With an estimated 25% of all traumatic deaths, chest trauma ranks second after head injury [3, 4]. Rib fractures are caused by high-energy trauma (HET) in the younger patients, often with concomitant injuries, and in the elderly as a result of low energy trauma (LET) [5–7]. Sustaining multiple rib fractures can result in a flail chest, defined as fracture of three or more consecutive ribs in two or more places, creating a flail segment [8, 9]. Patients may also have multiple simple rib fractures or a combination of both.

While open surgical fixation of rib fractures dates back to the 1940s, multiple rib fractures are routinely treated nonoperatively [10]. Nonoperative treatment includes pain management, oxygen support or mechanical ventilation, bronchodilator inhalers, and pulmonary physical therapy. Despite this treatment strategy, mortality and complications such as pulmonary contusion, hemopneumothorax, and pneumonia are seen in up to 34% and in 35–77% of patients, respectively [1, 2, 5, 6, 11–15]. Various studies have identified risk factors that increase mortality such as age and number of rib fractures [3, 6, 7, 11, 16–18].

Furthermore, at 2 years post-injury, up to 29% of patients have not yet returned full time to their pre-injury job and 64% of patients with isolated multiple rib fractures still experience chest wall pain [19, 20]. With incapacitating pain often accompanying traumatic rib fractures, epidural analgesics are suggested as the optimal analgesic for patients with multiple rib fractures. Two meta-analyses have shown that epidural use results in significant less pain but has no benefit regarding the length of both intensive care unit (ICU) and hospital stay, mortality, and complication rate, indicating the necessity of an optimized analgesic modality for rib fracture patients [21, 22].

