### Outcome measures

#### Primary outcome measure

The primary outcome measure is pneumonia within 30 days after trauma. In order to define pneumonia, the flowchart of the Centers of Disease Control and Prevention, based on imaging and clinical and laboratory criteria, will be followed (Fig. 1) [42]. Temperature (*T*) will be measured daily during admission. If *T* > 38.0 °C intra-auricular (or *T* > 39 °C rectal), bladder, central, or a sputum culture will be done. Also, the wound will be checked (if applicable) and a radiograph of the thorax will be made. If patients are suffering from fever at home, they will be advised to visit the outpatient clinic or emergency department. The temperature will be measured on arrival at the outpatient clinic or emergency department, and the same additional examinations will be performed. A monitor will independently review the patient’s medical files in order to ensure that the pneumonia was actually present.

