
### Other data collected

In addition to the outcome measures, the following data will be collected in order to assess similarity between the treatment groups:

Intrinsic variables (baseline characteristics): age, gender, body mass index (BMI), American Society of Anesthesiologists (ASA) grade, tobacco consumption, comorbidities, and medication use.

Injury-related variables: injury mechanism, pleura drain placed, number and location of rib fractures, affected side, presence of sternum fracture, additional injuries represented by the Abbreviated Injury Score (AIS) [53], and Injury Severity Score (ISS).

Intervention-related variables: surgical approach, number of plates and splints used and for which ribs, surgical delay, primary and secondary surgeon (resident or staff surgeon), wound drain, intra-operatively placed interpleural drain including duration of drainage, and duration of surgery.

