### Statistical analyses

Data will be analyzed using the Statistical Package for the Social Sciences (SPSS), version 24.0 or higher (SPSS, Chicago, IL, USA), and reported following the Consolidated Standards of Reporting Trials (CONSORT) guidelines. Normality of continuous data will be tested with the Shapiro-Wilk test. Homogeneity of variances will be tested using Levene’s test. The analysis will be performed on an intention to treat basis. A two-sided *p* value < 0.05 will be taken as threshold of statistical significance in all statistical tests. Procedures will be implemented to reduce missing data. In previous studies of the principal investigator’s department, these procedures led to < 5% missing data [54]. If necessary, missing values will be replaced using multiple imputation following the predictive mean matching method, using ten imputations.

Descriptive analysis will be performed in order to report the outcome measures for both treatment arms. For categorical data, numbers and frequencies will be reported. For continuous data, the mean and SD (parametric data) or the mean and percentiles (non-parametric data) will be reported.

Next, univariate analysis will be performed in order to test for statistical significance of differences between the primary and secondary outcome measures across the two groups. A chi-squared analysis or Fisher’s exact test will be used for statistical testing of categorical data (e.g., the primary outcome, pneumonia). Continuous data (i.e., hospital length of stay) will be tested using Student’s *t* test (parametric data; with equal variance or unequal variance whichever applies according to Levene’s test) or Mann-Whitney *U* test (non-parametric data).

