Multivariable analysis will be done as secondary analysis. A logistic regression model will be developed, with pneumonia as dependent variable and treatment as covariate. Nonoperative treatment will serve as reference category. Baseline and injury-related variables that may potentially confound the association between treatment and outcome will be included in this model as covariate. These will be selected from literature and from data of this study (see Other data collected). Known potential confounders according to literature data are the number of rib fractures and age. Other potential confounders collected as part of this study are gender, ASA, COPD, osteoporosis, and additional injuries (ISS ≥ 16 versus ISS < 16, and presence versus absence of severe injuries (AIS ≥ 3) for any body region). Variables that produce a *p* value < 0.2 in the univariate analysis will be included in the regression model. Odds ratios will be reported with their 95% confidence interval and *p* value.

Continuous outcomes repeatedly measured over time will be compared between treatment groups using linear mixed-effects regression models (with fixed effects for treatment and other covariates like gender and age, if applicable). The interaction between treatment and time will be included to test for differences between groups over time. For each follow-up moment, the estimated marginal mean will be computed per treatment group and compared post hoc with a Bonferroni test in order to correct for multiple testing.

Other continuous and binomial variables will be tested with multivariable linear and binary logistic regression models, respectively. The outcome measure will be entered as dependent variable and treatment as covariate. Nonoperative treatment will serve as the reference group. Baseline and injury-related variables that may potentially confound the association between treatment and outcome will be included in the models as covariate. Coefficients will be reported with their 95% confidence interval and *p* value.

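### The primary pneumonia test leaves out age and number of rib fractures, which the plan collects and singles out: a valid choice, but one that probably gives up a little power

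*Protocol article*

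**What the plan says.** The Primary outcome measure section fixes a binary endpoint: "The primary outcome measure is pneumonia within 30 days after trauma".

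The Statistical analyses section assigns this endpoint to the univariate step, where a chi-squared or Fisher's "exact test will be used for statistical testing of categorical data (e.g., the primary outcome, pneumonia"). Covariates come in later: "Multivariable analysis will be done as secondary analysis". That model is a logistic regression of pneumonia on treatment. Candidate covariates are screened at univariate p < 0.2, and odds ratios are reported.

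Two candidates are singled out: "Known potential confounders according to literature data are the number of rib fractures and age". Both are available before randomisation. Age is listed among the baseline characteristics. The injury-related variables in Other data collected include "number and location of rib fractures", and the schedule of events places a CT scan at screening. The Background mentions the same two factors, but for a different outcome: "Various studies have identified risk factors that increase mortality such as age and number of rib fractures".

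The Sample size calculation compares two raw proportions, 35% and 15%, with no covariates. Randomisation is 1:1 and stratified by site only.

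**The concern.** In a randomised trial, age and fracture count do not confound the treatment comparison. If they are related to pneumonia, they are prognostic factors, and adjusting for them makes the treatment comparison more precise. To call a variable a potential confounder of the association between treatment and pneumonia is to suppose that it may predict pneumonia. The plan therefore names two plausible prognostic variables, has both in hand before allocation, and leaves them out of the analysis on which its main conclusion rests.

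The secondary model does not fully make up for this. It is not primary, its covariates pass through a data-dependent screen, and its odds ratio is not on the risk-difference scale used to size the trial. What is at stake is power in a trial sized for 80%, with little to spare if losses reach the stated 25%.

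**Working it through.** **Inputs.** From Sample size calculation: 35% vs 15%, two-sided alpha 0.05, power 0.80, 72 per arm, 25% loss, 90 per arm randomised. The prognostic strength of the covariates for pneumonia is not given, so it is varied as an assumption: within-arm AUC from about 0.60 to 0.81, plus a case with no prognostic value.

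**Step 1: reproduce the plan's figure.** Pooled formula:

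n = [1.960 × √(2 × 0.25 × 0.75) + 0.8416 × √(0.35 × 0.65 + 0.15 × 0.85)]² / 0.20²
= (1.2002 + 0.5014)² / 0.04 = 72.4 per arm.

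This is 73 rounded up, against 72 stated, so the figure reproduces.

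**Step 2: power without covariates.** Power = Φ[(0.20 × √n − 1.2002) / 0.5958].
- n = 72: Φ(0.834) = 79.8%. Exact enumeration gives 81.0% for the uncorrected chi-squared test and 74.7% for Fisher's test. The chi-squared test is the comparator below.
- n = 90 × 0.75 = 67.5: Φ(0.743) = 77.1%.

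**Step 3: power with covariates, by simulation.** There were 10,000 trials per setting at 72 per arm. Two independent normal baseline covariates acted through a logistic model, with the marginal rates held at 35% and 15%.

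| AUC (assumed) | Chi-squared | Adjusted, likelihood-ratio | Adjusted, Wald |
|---|---|---|---|
| no prognostic value | 80.9% | 80.6% | 79.5% |
| 0.60 | 81.2% | 81.9% | 81.0% |
| 0.68 | 80.4% | 83.3% | 82.3% |
| 0.74 | 80.2% | 85.6% | 84.7% |
| 0.81 | 81.2% | 90.3% | 89.4% |

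At 68 per arm and AUC 0.74, power rises from 77.4% to 83.8% (likelihood-ratio) or 82.9% (Wald).

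**Step 4: the estimator recommended below.** This is the standardised risk difference from the logistic model, with an influence-function standard error and 4,000 trials per setting.

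| Per arm | AUC (assumed) | Unadjusted | Standardised risk difference | Gain (points) |
|---|---|---|---|---|
| 72 | 0.62 | 80.9% | 81.6% | 0.7 |
| 72 | 0.66 | 81.3% | 83.7% | 2.4 |
| 72 | 0.72 | 80.6% | 85.0% | 4.4 |
| 72 | 0.79 | 81.4% | 88.8% | 7.4 |
| 68 | 0.67 | 77.8% | 80.9% | 3.1 |
| 68 | 0.73 | 77.1% | 82.9% | 5.8 |

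**Step 5: type I error at 72 per arm.**
- Likelihood-ratio and Wald tests: 4.8% to 5.3% in 10,000 runs. A smaller simulation of 4,000 runs gave 5.6% to 5.8% for the likelihood-ratio test, against 5.1% to 5.4% unadjusted.
- Standardised risk difference: 5.2% to 5.5%, against 5.4% to 5.6% unadjusted. Two further simulations gave 5.2% to 5.9% (unadjusted 5.0% to 5.9%) and 5.3% to 6.2%.

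The adjusted test is therefore close to nominal, perhaps slightly liberal at this size, and a small part of the gain may come from that.

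**The case against.** The strongest reply is that nothing here is wrong. A chi-squared test in a 1:1 randomised trial is valid, it matches the way the trial was sized, and an adjusted model is already planned. That stands: the question is which of two valid analyses should be primary.

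The reply also has force on size. No figure is given for how well these variables predict pneumonia. Eligibility may narrow their range, since it requires three simple fractures among ribs 4 to 10 and excludes flail chest and patients unfit for surgery. The gain may therefore lie at the low end.

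Three stronger readings are tempting, and the document supports none of them:
- **That a chance imbalance in age or fracture count would pass straight into the primary result.** The 5% error rate of the unadjusted test already allows for chance imbalance, and the plan both compares the groups on these variables and adjusts for them secondarily.
- **That the plan treats the two variables as established predictors of pneumonia.** It calls them potential confounders, and the Background links them to mortality.
- **That a single power figure can be quoted after adjustment.** This would need a covariate–outcome correlation that the document does not give.

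Nor does it count against the plan that no reason is given for the unadjusted choice. A condensed article commonly leaves that to the full documents.

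**Conclusion.** The point holds as a matter of efficiency. At 72 per arm, adjusting for the two covariates adds about 0 to 1 point of power if they are weak (AUC about 0.60), 2 to 5 points if moderate (0.66 to 0.74), and 7 to 9 points only if strong (about 0.80). With no prognostic value it costs up to about 1 point: 0.3 by likelihood-ratio, 1.4 by Wald, and under 1 for the standardised risk difference. These gains rest on an assumed prognostic strength and on the plan's own event rates.

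The balance favours adjustment because the possible loss is small and the possible gain is larger. If 25% of patients are lost, moderately prognostic covariates would bring power back to about 80% or slightly above. The primary test as planned remains valid and unbiased, so this is a cheap improvement and not the correction of an error.

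**What to change.** Before database lock, and without reference to outcome data by arm, specify the following:
- **Primary analysis:** logistic regression of pneumonia on allocated treatment, with age and number of rib fractures as continuous covariates that are always included and exempt from the p < 0.2 screen.
- **Reported result:** the standardised (marginal) risk difference, with 95% CI and p value from that same estimator, so that the result stays on the 35% vs 15% scale.
- **Sensitivity analysis:** the unadjusted chi-squared test.

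The cost is a sentence or two in the analysis section, with no new data and no extra patients. The downsides are two more parameters against about 36 expected events (72 × 0.35 + 72 × 0.15 = 25.2 + 10.8), or 12 events for each of the three slopes, and a primary result slightly less simple to present than a two-by-two table.

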### Recruitment and randomization

Eligible persons presenting to the emergency department (ED) or referred from another hospital, with multiple, simple rib fractures will be informed about the trial at the ED or at the surgical ward after admission. After explanation of the study, eligible patients will receive written information and a consent form from the attending physician, the clinical investigator, or a research assistant. Patients meeting all eligibility criteria will be recruited within 1 day after hospital admission. As surgical rib fixation appears to be most beneficial when performed within 72 h after trauma, patients are stimulated to decide within this period. However, informed consent can be given by the patient as long as rib fixation can be carried out within 1 week after trauma. Should patients not be able to sign informed consent themselves, a legal representative will receive oral and written information about the study, in the hospital, by the attending physician, the clinical investigator, or a research assistant, and will be asked to consent with participation of the patient.

After signing informed consent by patient or proxy, participants are allocated to one of the two study arms (surgical stabilization or nonoperative treatment) using a web-based randomization program that will be available 24 h a day. Allocation will be at random and concealed, in a 1:1 ratio, and will be stratified by site. Variable block sizes will be used; in each block, both treatments will be represented equally. As the intervention cannot be blinded, it will in no case be necessary to break the randomization code.

As with many surgical trials, patients and surgeons cannot be blinded for the intervention. In order to reduce bias as much as possible, a research physician or research assistant will perform the follow-up measurements using a standardized protocol. Also, the treating surgeon or ICU doctor will identify the primary outcome (i.e., pneumonia) based on the definition as mentioned under outcome measures.

Participation is on a voluntary basis and participants are allowed to withdraw from the study at any time without specifying why. The general practitioner will be informed about the patients’ participation.

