## Nonoperative allocation

Nonoperative treatment will consist of optimal pain treatment, supportive oxygen or ventilation if needed, early mobilization, Salbutamol/Atrovent spray, and physical therapy for optimizing ventilation. Without definitive proof for the best protocol, each participating center is allowed to use its local protocol for interpleural drainage use, mechanical ventilation, and pain control. Although this may introduce some heterogeneity across hospitals, it benefits extrapolation of the results. Critical elements of the nonoperative treatment will be recorded.

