### Sample size calculation

Calculation of the required sample size for the primary analysis is based on data from a Cochrane review and a large retrospective analysis [7, 32]. These studies suggest a pneumonia rate of 35% in nonoperatively treated patients and 15% in operatively treated patients with multiple rib fractures. This difference is considered clinically relevant. A two-sided test with an α level of 0.05 and a β level of 0.2 requires 72 patients in each group. In order to account for 25% loss of patients to follow-up and mortality, a sample size of 90 patients per group is needed. In total, 180 patients will be included and randomized.

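### Allocation is stratified by site, but the primary pneumonia test is unstratified and no named model covariate is site; if sites differ, the test is conservative

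*Protocol article*

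**What the plan says.** - **Design.** Under Trial design and setting, 12 hospitals take part. Under Recruitment and randomization: "Allocation will be at random and concealed, in a 1:1 ratio, and will be stratified by site". On blocking: "Variable block sizes will be used; in each block, both treatments will be represented equally". Site is the only stratification factor.
- **Care by site.** Under Nonoperative allocation, "each participating center is allowed to use its local protocol for interpleural drainage use, mechanical ventilation, and pain control". The same paragraph accepts that this may bring some heterogeneity between hospitals.
- **Primary analysis.** Under Statistical analyses, in the paragraph on univariate analysis, a chi-squared or Fisher's exact "test will be used for statistical testing of categorical data (e.g., the primary outcome, pneumonia"). Continuous outcomes get a t test or Mann-Whitney test, also without site.
- **Models.** The logistic model for pneumonia is secondary. Its named candidate covariates are number of rib fractures, age, gender, ASA, COPD, osteoporosis and injury severity. The other linear and logistic models take baseline and injury-related variables. The mixed models give gender and age only as examples. Site is named in none of these, nor under Other data collected.

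**The concern.** Blocking within site nearly balances the arms in each hospital, so differences between hospitals largely cancel out of the treatment comparison. A pooled 2×2 test does not use this: its variance still contains the between-site variation. If sites differ in pneumonia risk, the standard error is too large and the p value too high for the randomisation that was carried out.

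The protocol gives a reason to expect some difference, because ventilation, drainage and pain control follow local practice. Those practices may bear even more directly on secondary outcomes such as ventilation days, analgesic use and length of stay.

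This is not a detail left to an unseen plan. The article itself fixes the primary test and names the types of covariate.

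**Working it through.** **Step 1. Reproduce the plan's own figure.** Inputs from Sample size calculation: "These studies suggest a pneumonia rate of 35% in nonoperatively treated patients and 15% in operatively treated patients with multiple rib fractures"; "A two-sided test with an α level of 0.05 and a β level of 0.2 requires 72 patients in each group". Pooled-variance formula, no continuity correction, mean rate 0.25:

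n = [1.96·√(2·0.25·0.75) + 0.842·√(0.35·0.65 + 0.15·0.85)]² / 0.20² = (1.200 + 0.501)² / 0.04 ≈ 72.4

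This is 73 rounded up, against the stated 72. The sample size therefore rests on an unstratified comparison of two proportions, which matches the primary test.

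**Step 2. Evaluable patients.** The article plans 90 per group with 25% loss: 90 × 0.75 = 67.5 per group. At 68 per group the same formula gives 77.4% power; at 90 per group it gives 87.9%. The effect of site is therefore shown for both cases.

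**Step 3. The two tests.**

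- Pooled: z = (p₁ − p₀) / √[p̄(1 − p̄)(1/N₁ + 1/N₀)]
- CMH over sites k: z = Σ(x₁ₖ − n₁ₖmₖ/nₖ) / √Σ[n₁ₖn₀ₖmₖ(nₖ − mₖ) / (nₖ²(nₖ − 1))]

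Here mₖ is the number of events at site k and nₖ the number of patients there.

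**Step 4. Simulation.** There are 12 unequal sites (6 to 30 patients), 180 randomised, and near-balanced blocks within site. A normal site effect acts on the logit scale, with the marginal rates held fixed. The between-site SD is an assumption, because the article gives none. For scale, with a median site at 25%, one SD either side is:

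- SD 0.5: logit −1.10 ± 0.5, or about 17% to 35% (ICC = 0.25/(0.25 + 3.29) = 0.07)
- SD 1.0: logit −1.10 ± 1.0, or about 11% to 48% (ICC = 1/(1 + 3.29) = 0.23)

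All 180 evaluable, pooled vs CMH:

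| Between-site SD | Type I error | Power, 35% vs 15% |
|---|---|---|
| 0.5 | 4.5% vs 5.0% | 88.9% vs 89.6% |
| 1.0 | 3.4% vs 4.8% | 89.4% vs 91.9% |

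Other site-size patterns and seeds put the pooled type I error at SD 1.0 between 3.4% and 3.9%.

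25% random loss, 60,000 runs per cell (Monte Carlo SE about 0.2 points), power for pooled vs CMH without continuity correction:

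| Between-site SD | Pooled | CMH | Difference |
|---|---|---|---|
| 0 | 78.0% | 76.5% | −1.5 |
| 0.25 | 78.0% | 76.9% | −1.1 |
| 0.5 | 78.4% | 78.3% | −0.1 |
| 1.0 | 78.8% | 81.9% | +3.1 |

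A repeat with a different seed and site sizes gave −1.7, −1.4, −0.4 and +2.8 points.

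**Step 5. Two features of the remedy.** A continuity-corrected CMH test costs a further 6 to 7 points under 25% loss. At SD 1.0 it reaches only 75.4%, below the pooled test's 78.8%. With very uneven recruitment (sites of 2 to 50) and 25% loss, uncorrected CMH gives 76.2% vs 78.0% at SD 0 and 77.5% vs 78.0% at SD 0.5.

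**Step 6. Continuous outcomes.** Ignoring site widens the standard error by about 1/√(1 − ICC): 5.4% at ICC 0.10 and 11.8% at ICC 0.20 (ICCs assumed).

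**The case against.** The strongest reply is that the premise is inferred. The article reports no between-site variation in pneumonia. Supportive care before and after surgery is the same as in the control arm, pneumonia follows one CDC flowchart, and a monitor reviews the files. The sample size and the primary test agree with each other. The pooled test does not raise the false-positive rate, and at low site variation the stratified test is the weaker one. All of this stands, and it limits the point to calibration.

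A reader might infer four stronger things that the article does not support:

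- **That the trial loses power by ignoring site.** Under the planned loss this appears only when site variation is well above SD 0.5. Below that, stratifying costs power.
- **That the primary result would be invalid.** Type I error stays at or below about 5% in every scenario.
- **That every secondary model excludes site.** The mixed-model covariate list is open, so site is unnamed there rather than ruled out.
- **That no interval is planned for pneumonia.** Odds ratios with 95% CIs are promised, though only from the secondary logistic model with covariates screened at p < 0.2.

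The reply does not remove the mismatch itself: the one factor used to stratify allocation is absent from the test that decides the trial.

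**Conclusion.** The point holds in a limited form. The stated primary analysis does not reflect the stated randomisation. If sites differ in pneumonia risk, the pooled test is conservative: about 4.5% type I error at SD 0.5 and 3.4% at SD 1.0, with 180 evaluable. The net effect on power under 25% loss runs from a loss of about 1.5 points to a gain of about 3 points for the stratified test.

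These sizes rest on an assumed logit-normal site effect, assumed site sizes, and loss unrelated to arm, site or outcome. The direction of the type I error effect rests only on sites differing. This is a cheap improvement, worth making before data are seen.

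**What to change.** 1. Make the primary analysis a CMH test stratified by site, stated to be without continuity correction. Check which version the software prints.
2. Fix in advance, without reference to outcomes, a rule for pooling very small sites into one stratum.
3. Report a site-stratified risk difference with 95% CI as the primary effect estimate.
4. Keep the unstratified chi-squared test as a sensitivity analysis.
5. Name site as a random intercept in the secondary logistic, linear and mixed models. With about 180/12 = 15 patients per site, 11 site indicators in an ordinary logistic model would be a poor alternative.

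**Cost.** Only the analysis wording changes: no new data and no change to conduct. The downside is about 1 to 1.5 points of power if sites do not differ, and slightly more (1.8 points in the sites-of-2-to-50 scenario) if recruitment is very uneven and small sites are not pooled.

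### The secondary adjusted model offers injury severity only as two yes/no cuts (ISS ≥ 16, any AIS ≥ 3), although the scores are collected; continuous ISS would keep more information with fewer parameters

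*Protocol article*

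**What the plan says.** The Protocol article, Other data collected, lists among the injury-related variables "additional injuries represented by the Abbreviated Injury Score (AIS) [53], and Injury Severity Score (ISS"). It names no threshold for either score.

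Statistical analyses then describes an adjusted logistic model for pneumonia and gives its status: "Multivariable analysis will be done as secondary analysis". Candidate covariates come in two groups. From the literature: "Known potential confounders according to literature data are the number of rib fractures and age". From the study's own data: "Other potential confounders collected as part of this study are gender, ASA, COPD, osteoporosis, and additional injuries". The last item is then specified as two indicators: "additional injuries (ISS ≥ 16 versus ISS < 16, and presence versus absence of severe injuries (AIS ≥ 3) for any body region").

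Entry into the model is conditional: "Variables that produce a *p* value < 0.2 in the univariate analysis will be included in the regression model". No reason is given for the cut points. The primary comparison is a separate unadjusted chi-squared or Fisher's exact test.

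**The concern.** The article does not leave the coding of injury severity open. It fixes two dichotomies for scores that it also says are collected. Cutting a graded score treats all patients on one side of the threshold as equal, so the model explains less of the outcome variation due to severity and corrects less well for a chance imbalance between the arms.

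The two cuts also overlap heavily. If they are nested, they carry one ordered three-level variable in two parameters, and their odds ratios become awkward to read. With both in the model, the ISS odds ratio compares patients only among those who already have an AIS ≥ 3. The model will have few events, so candidate parameters are worth saving where this loses nothing important.

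**Working it through.** The plan gives no figure for this coding. Its event rates supply the background: "a pneumonia rate of 35% in nonoperatively treated patients and 15% in operatively treated patients with multiple rib fractures". With two-sided α 0.05 and 80% power, the pooled normal approximation gives 73 per group against the stated 72 (power at 72 is 79.8%), so the design inputs are understood correctly.

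**1. Are the cuts nested?** Assumption: ISS is the sum of squares of the three highest regional AIS values.
- With every AIS ≤ 2, the largest ISS is 3 × 2² = 12, which is below 16. Enumerating all combinations of six regions with AIS 0 to 5 gives no case with ISS ≥ 16 and no AIS ≥ 3. If the thorax counts, ISS ≥ 16 is a subset of AIS ≥ 3, and only three levels exist.
- If the thorax is excluded from the AIS indicator, thorax 3 with two other regions at 2 gives ISS = 9 + 4 + 4 = 17 and no counted AIS ≥ 3. Nesting then fails, although overlap remains.

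**2. How much information do the cuts keep?** Assumption: the effect of ISS is linear.
- One cut at quantile q of a normal score keeps φ(z)² / [q(1 − q)]. At q = 0.5 this is 0.3989² / 0.25 = 0.64. At q = 0.8 it is 0.2800² / 0.16 = 0.49. The loss is 36% to 51%.
- The best two cuts of a normal score keep 0.81.
- ISS is not normal, so simulated ISS distributions (assumed, not from the documents) were also used. There the two indicators together kept 0.71 in one and about 0.64 in another.
- Across these cases, two cuts lose roughly 20–35%.
- In a further simulated case, the chest injury alone was coded AIS ≥ 3 in every patient. The AIS indicator is then constant, only the ISS cut works, and 0.60 is kept. That 40% loss lies within the single-cut range.

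**3. How many parameters and events?** Candidates plus treatment: treatment, number of rib fractures, age, gender, ASA (counted as one), COPD, osteoporosis, ISS ≥ 16 and AIS ≥ 3, which makes 9. One linear ISS term in place of both indicators makes 8. The mean planned pneumonia rate is (0.35 + 0.15) / 2 = 0.25.

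| Patients analysed | Expected events | Events per candidate, 9 | Events per candidate, 8 |
|---|---|---|---|
| 180 | 45 | 5.0 | 5.6 |
| 144 (2 × 72) | 36 | 4.0 | 4.5 |
| 135 (180 × 0.75) | 33.75 | 3.75 | 4.2 |

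**4. What does it do to the treatment comparison?** Simulation with N = 180, 35% versus 15%, an assumed ISS distribution and a truly linear ISS effect gave this power for treatment:

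| Log odds ratio per SD of ISS | Linear ISS | Two indicators |
|---|---|---|
| 0.3 | 88.3% | 88.3% |
| 0.5 | 89.5% | 89.0% |
| 0.8 | 91.9% | 90.1% |

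A second simulation of the same kind put the advantage of continuous ISS at about 0.3 to 2.5 percentage points.

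**The case against.** The strongest reply is that this is a choice between defensible codings in a secondary model. Several parts of it stand.

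- Two nested indicators are a valid ordinal coding, not an error.
- ISS does not determine whether any region is severely injured. ISS 9 arises from a single AIS 3 and also from 2, 2, 1. The pattern 2, 2, 2 scores 12 with no severe region, above a lone AIS 3 at 9. Dropping the AIS indicator therefore loses some single-region information.
- A linear term is itself an assumption about shape, and a spline would use up the saved parameter.
- The effect on the treatment comparison is small even when the simulation favours linear ISS.

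A reader might also infer more than the article supports. One inference is that both indicators are certain to be in a nine-parameter model. They are candidates under the p < 0.2 screen, and nine is the candidate count. Another is that every patient with ISS ≥ 16 must be positive on the AIS indicator. The item is headed as additional injuries, and Other data collected uses the same phrase ("additional injuries represented by the Abbreviated Injury Score (AIS"), which may mean injuries beyond the thorax. The reference to any body region points the other way, and the article does not settle it. A third is that age and number of rib fractures are also dichotomised; the article does not cut either of them.

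The reply does not justify using only the cuts. The scores are collected, no reason is given for the thresholds, and a graded covariate is generally the better default for adjustment.

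**Conclusion.** The point holds as a minor improvement. The article offers injury severity to the secondary model only in dichotomised form, at an estimated loss of roughly 20–35% of the information in ISS with both cuts, or 36–51% if only one survives screening. It uses one more candidate parameter than needed, with about 34–45 expected events. These figures rest on a linear ISS effect, on normal or assumed ISS distributions and, for the parameter count, on ASA entering as one term. Strict nesting further requires the usual ISS definition and a thorax that counts as a body region.

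It would be wrong to infer that the trial's main conclusion is at risk. The primary test is unadjusted and the sample size does not depend on this model. Because treatment is randomised, the cost is some precision and some residual chance imbalance, not systematic confounding. Nor does the change solve the shortage of events: events per candidate parameter rise only from 5.0 to 5.6, or from 3.75 to 4.2.

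**What to change.** Before the data are analysed, pre-specify ISS as a continuous covariate in place of the ISS ≥ 16 cut. Drop the AIS ≥ 3 indicator unless it is wanted as a separate term for severe injury of a single region. If it is kept, state whether the thorax counts. Both cuts can remain in descriptive tables.

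The scores are already collected, so the cost is a change of wording. The downside is the linearity assumption for ISS. A pre-specified spline would relax it but would use up the parameter saved.
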